### Sample size

The estimated number of client participants required to achieve the study objective is 30–40. This number is considered adequate to provide sufficient variation and to ensure valuable insights into the feasibility aspects assessed in this study.^37^ In feasibility studies, formal sample size calculations are rarely required, as statistical powering of future trials based on such studies is often unreliable.^37 39 40^ Instead, recommended practice is to recruit a sample that is large enough to capture variability in participant characteristics and to identify potential barriers to implementation. The chosen sample size of 30–40 participants is therefore deemed sufficient for these purposes while remaining feasible within the scope of the project.

### Recruitment

Potential clients can receive information in different ways from the involved healthcare settings. The healthcare staff can give a short oral briefing about the intervention programme and study during visits or telephone calls. Alternatively, information is provided via brochures and screens in the waiting rooms. Those who are interested in participation receive an information letter with complete details about the study. If they agree to participate, they send the informed consent (online supplemental material S3) to the researchers.

Once the researchers receive the consent form, potential participants are contacted by telephone. The content of the information letter is presented orally, and the potential participants are given the opportunity to ask questions to confirm their consent. They are then screened for the inclusion criteria, and if they meet the criteria, baseline assessments are initiated.

Personnel at the involved healthcare settings, including OTs, managers and other involved staff, receive oral and written information about the project before their written informed consent is sought. OTs and managers who are interested in being included in the study are asked if they would like to contribute, in addition to recruiting clients, by delivering SEE. Thus, SEE 2.0 will be delivered by OTs who want to deliver the new intervention and complete the educational programme.

### Data collection

An overview of the timeline of the various methods used to collect data from clients, OTs, managers and other staff is presented in online supplemental table S2. Outcome assessments will be conducted at baseline and at 4 and 12 months postintervention. Additionally, at 4 months, clients will rate the acceptability and value of SEE 2.0. Intervention adherence will be evaluated by forms and field notes throughout the intervention. Qualitative experiences of the programme will be gathered through semistructured interviews with clients and FG discussions with staff.

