**Methods and analysis:**

This feasibility study employs a pretest and post-test design with no control group, embedded within a mixed-method approach. The participants will include 30–40 clients, occupational therapists and managers involved in delivering SEE 2.0 in primary healthcare and hospital-based services. Data will be collected through assessments and forms at baseline, 4 months and 12 months after inclusion. Additionally, qualitative methods will be used to enhance the understanding of participants’ experiences.

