
### Objectives

The project aims to evaluate the feasibility and implementation potential of SEE 2.0 for people with long-term health conditions across selected primary care and hospital-based services in Sweden. The following objectives were defined to assess SEE 2.0 and the study design:

Evaluate participant recruitment and retention.Evaluate the assessments’ suitability to detect outcomes of SEE at 4 and 12 months after entry into the programme, as well as the acceptability of the assessments.Evaluate client participants’ acceptability and value of SEE.Explore client participants’ experiences with the SEE intervention process and its influence on their self-management, everyday life and health.Evaluate participant (client and OT) adherence to SEE.Explore OTs’ and managers’ experiences of feasibility, acceptability, value and implementation potential of deliver SEE across different healthcare settings.

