The internet-based SEE 2.0 intervention is person-centred and evolves through several phases, each comprising one or more modules.^4 32^ Throughout the entire intervention process, an OT continuously supports clients’ self-directed activities and change process related to each module by providing written feedback (asynchronous) and guided dialogues (synchronous), both delivered online. In the first web module in the intervention process, clients are supported in exploring their motivation and readiness to implement changes in their everyday activities. This is followed by an in-depth dialogue with an OT to further address these issues. Subsequently, clients engage in self-analysis by completing assessments of their activity engagement and use of management strategies. Their findings are further explored in one to two meetings in guided dialogues with the OT. Next, clients complete six web modules one at a time, each including concise educational videos accompanied by self-analyses and reflective tasks. Their work across the modules is supported by written feedback from the OT and by three guided in-depth dialogues with the OT, held at selected points during the process. The six modules aim to enhance self-management by imparting knowledge about strategies and modifications for everyday activities that can prevent disability and promote health. When clients have completed all modules and dialogues with the OTs, together, they create an activity plan for how to change their everyday life, including specific goals and activity-based management strategies to achieve an active everyday life (approximately 3–4 weeks into the programme). Clients receive ongoing support from the OT when the plan is implemented, using a person-centred approach that includes follow-up meetings tailored to their needs. The intervention process is expected to last between 2 and 4 months, but clients’ process of change can continue also when the intervention has come to an end. The OT also contacts and coordinates with other professionals if needed to implement the plan. The intervention process is complemented by written client materials introducing the intervention process as well as summarising and repeating important content from the web modules.

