### Participant timeline

The study timeline is illustrated in the online supplemental table S2. The enrolment of the client participants began in September 2024 and is expected to be completed by December 2026. The person-centred intervention process is anticipated to vary between 2 and 4 months. Clients’ change processes and subsequent improvements are expected to continue even after the interventions end. Consequently, to identify potential long-term outcomes, evaluations will be conducted 4 months and 12 months after the start of SEE 2.0.

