### Data analysis

The statistical analysis will assess the suitability of the assessments in detecting outcomes of SEE 2.0 at 4 and 12 months after entry into the programme. In this study, descriptive statistics and non-parametric tests will be used to identify patterns of changes and compare outcomes on respective outcome assessments over time, from baseline to 4 and 12 months. The intention-to-treat approach will be applied, and per-protocol analyses will be conducted if necessary. A gender perspective will be considered in the data analysis to identify potential differences and similarities in outcomes. Sociodemographic characteristics in relation to outcomes will be analysed descriptively. The significance level will be set at p<0.05 for all the statistical tests. All the data from the enrolment process, the number of complete or incomplete assessments, study-specific forms for adherence, acceptability, value, potential harms and field notes will be compiled descriptively^38 66^ by analysis of content and descriptive statistics. The qualitative interviews with the clients will be analysed using the constant comparative method of grounded theory,^61^ as this method is suitable for identifying patterns in interactions, strategies and processes such as intervention processes. The FG discussions will be analysed with FG analysis^63 64^ to identify themes in the collective experiences.

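### Data collection times the outcome assessments from the end of the intervention, but the objectives, timeline and analysis count from the start of SEE 2.0: a shift of 2 to 4 months for a given client

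*Protocol article*

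**What the plan says.** The protocol article gives the follow-up schedule in five places.

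- Data collection: "Outcome assessments will be conducted at baseline and at 4 and 12 months postintervention". The next sentence places the client ratings of acceptability and value at 4 months, without a separate anchor.
- Objectives, second objective: the assessments' "suitability to detect outcomes of SEE at 4 and 12 months after entry into the programme".
- Participant timeline: "evaluations will be conducted 4 months and 12 months after the start of SEE 2.0".
- Data analysis: suitability "in detecting outcomes of SEE 2.0 at 4 and 12 months after entry into the programme".
- Abstract, Methods and analysis: "Data will be collected through assessments and forms at baseline, 4 months and 12 months after inclusion".

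The length of the intervention is given twice and consistently. The section on the client programme says "The intervention process is expected to last between 2 and 4 months", and Participant timeline says "The person-centred intervention process is anticipated to vary between 2 and 4 months".

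Data collection and Participant timeline both refer to supplemental table S2 for the schedule. That table is not among the documents at hand.

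**The concern.** An intervention that lasts months has a start and an end that are months apart, so 4 months after one is not 4 months after the other. The section that describes how data are gathered uses the end. The sections that state what is to be learned, when clients are seen and how the data are analysed use the start.

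The study has no control group. Its only outcome comparison is baseline against the 4- and 12-month values, so time zero is part of the definition of each follow-up outcome, including the primary outcome of engagement in activities. Participant timeline expects clients to go on improving after the intervention ends, so a shift of some months may change what is measured. Three further items depend on the anchor:

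- The acceptability, value and harm forms travel with the 4-month questionnaire (Acceptability and value of SEE 2.0).
- The PSS-10 asks about the past month. For a client who takes 4 months, a visit 4 months after start covers programme time only, while a visit 4 months after the end covers none of it.
- Retention to the last visit would be judged over a longer period from start.

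**Working it through.** No sample size, power or significance calculation bears on this point. The check is date arithmetic.

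**Inputs**

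- Nominal visits: 4 and 12 months (all five places listed above).
- Intervention length L: 2 to 4 months, varying by client (client programme section; Participant timeline).

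**Step 1. Time since start, if visits are counted from the end (Data collection)**

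- First visit: 4 + L = 4 + 2 to 4 + 4 = 6 to 8 months after start.
- Second visit: 12 + L = 12 + 2 to 12 + 4 = 14 to 16 months after start.

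**Step 2. Time since end, if visits are counted from the start (Objectives, Participant timeline, Data analysis)**

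- First visit: 4 − L = 4 − 4 to 4 − 2 = 0 to 2 months after the end.
- Second visit: 12 − L = 12 − 4 to 12 − 2 = 8 to 10 months after the end.

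| Anchor | Visit | Months since start | Months since end |
|---|---|---|---|
| Start or entry | 4 months | 4 | 0 to 2 |
| Start or entry | 12 months | 12 | 8 to 10 |
| End of intervention | 4 months | 6 to 8 | 4 |
| End of intervention | 12 months | 14 to 16 | 12 |

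**Step 3. Difference between the two readings for one client**

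(4 + L) − 4 = L and (12 + L) − 12 = L, so 2 to 4 months at each visit. Relative to the nominal interval this is 2/4 to 4/4 = 50% to 100% at the first visit, and 2/12 to 4/12 = about 17% to 33% at the second.

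**Step 4. Spread between clients within one reading**

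The range of L is 4 − 2 = 2 months. Counted from the end, clients differ by at most 2 months in time since start. Counted from the start, they differ by at most 2 months in time since the end.

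**Step 5. Inclusion against start**

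Under Recruitment, baseline assessments begin after consent and screening. Under Suitability and acceptability of outcome assessments, questionnaires go out by post and the SDO interview is arranged once they are returned. The article gives no interval from inclusion to the start of SEE 2.0, so no figure can be put on that difference.

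**The case against.** The best reply is that this is one wrong word. Three sections agree on start or entry. Participant timeline also gives the reason: the process varies in length and change continues afterwards, so evaluations are set at fixed times from the start. Client experiences of SEE 2.0 points the same way, since it places the second interview, held after completion, 4 to 5 months after the start. Table S2 may state the schedule outright. All of this stands, and it makes a slip in Data collection the likely explanation. It does not remove the need to correct the sentence, because no visible text says which anchor governs.

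A second reply is that the study is a small feasibility study, with 30 to 40 clients and mostly descriptive analysis, and that it already limits its claims about effects. That tempers the consequence. It does not change the fact that objective 2 names timepoints which Data collection, read literally, would miss.

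Three stronger readings are tempting, and the documents do not support them.

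- A reader might infer that clients will be measured 2 to 4 months apart from one another. That figure is the gap between two readings for the same client. It would become a difference between clients only if staff mixed anchors, and nothing in the article suggests that they do.
- A reader might count inclusion, entry and start as separate zero points with a material lag between them. They may be loose terms for nearly the same moment, and no interval is given.
- A reader might conclude that clients who take 4 months will rate the programme before finishing it. Counted from start, such a client answers at the point of finishing. An earlier rating would depend on the unquantified lag after inclusion.

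**Conclusion.** The point holds as an internal contradiction in the current text. Data collection and the sections on objectives, timeline and analysis cannot all be right, and the difference is 2 to 4 months for a given client at each follow-up visit. It is worth correcting, although probably a slip, because it fixes when the primary outcome and the 4-month forms are collected in a study whose only comparison is over time.

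The size rests on the stated intervention length of 2 to 4 months. It would grow for any client who takes longer. The conclusion assumes that table S2, which has not been seen, does not already settle the matter. If it does, the correction is purely textual. Nothing in the documents shows that any client has been assessed on the wrong date.

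**What to change.** 1. Reconcile Data collection and the abstract with Objectives, Participant timeline and Data analysis, and check all of them against supplemental table S2. Count every assessment, including the 4-month acceptability, value and harm forms, from one zero point: the start of, or entry into, SEE 2.0. Use one term for it throughout.
2. Report the time from the end of the intervention to each assessment. Completion is already a data-collection point, through the structured interview with the occupational therapist under Intervention adherence. The article does not say whether the date itself is noted, so confirm that it is. This route does not need platform data, which matters because the researchers have no access to 1177 (Ethics and dissemination).
3. If any client has been assessed under another anchor, tabulate the actual timing for those clients.

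The cost is a wording correction and, at most, one date per client on a form already in use. Enrolment is expected to run to December 2026, so the correction can still guide visits that lie ahead.

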#### Enrolment and retention

The enrolment, inclusion, retention and drop-out rates of the participants will be measured by the researchers during the study period.

#### Suitability and acceptability of outcome assessments

To evaluate the assessments’ suitability for detecting the outcomes of SEE 2.0 and their acceptability, responses to the assessments and complete and incomplete assessments, including missing values, will be registered. The primary outcome is engagement in activities, and potential improvements will be assessed from different perspectives. Satisfaction with Daily Occupations-Occupational Balance (SDO-OB)^47 48^ is an interview-based questionnaire that, in 13 items, addresses the activity level (ranging from 0 to 13), satisfaction with daily activities (ranging from 13 to 91) and general balance in activities from a time allocation perspective (five response alternatives ranging from −2 to +2). The Occupational Balance Questionnaire (OBQ-11)^49^ is a self-report questionnaire assessing balance in activities consisting of 11 items, each rated on a 4-point Likert scale. The scores are summed to yield a total score ranging from 0 to 33 points. The Occupational Value Assessment with Predefined items (Oval-pd)^50 51^ is a self-report questionnaire that assesses the perception of occupational value. The Oval-pd includes 18 items rated on a 4-point Likert scale, with total scores ranging from 18 to 72.

The secondary outcomes focus on aspects such as work ability, health and symptoms. The Work Ability Index (WAI) assesses self-perceived work ability on a 10-point ordinal scale. It also uses a 5-point Likert scale to evaluate the physiological and psychological demands of work. A higher score signifies a higher level of perceived work ability.^52^ A question will be used to assess work ability and sick leave percentage. Three items from the Life Satisfaction Questionnaire (LiSat-11) will be used to assess satisfaction with life as a whole, physiological health and psychological health. These self-reports will be assessed using a 6-point Likert scale (1=very dissatisfied, 6=very satisfied).^53 54^ The EuroQol Visual Analogue Scale (EQ VAS)^55^ will be used to assess health-related quality of life. The EQ VAS is a vertical scale ranging from 0 to 100, with 0 representing the ‘worst possible health state’ and 100 representing the ‘best possible health state’. A mark on the scale represents an individual’s current overall health status based on his or her own perceptions. The RAND-36 health survey^56^ is a self-report questionnaire that assesses functioning and well-being across 36 items in eight dimensions, each ranging from 0 to 100.

To assess self-related belief in one’s ability to effectively deal with stressful situations, the General Self-Efficacy Scale (GSE-10) will be used. The GSE-10 consists of 10 items, each scored on a 4-point Likert scale. The total score ranges from 10 to 40, with specific cut-offs indicating different levels of self-efficacy.^57^ The Perceived Stress Scale (PSS-10)^58^ will measure self-reported stress perceptions over the past month with 10 items, which are summed to range from 0 to 40. The Mental Fatigue Scale (MFS)^59^ contains 15 items for self-reporting of affective, cognitive and sensory symptoms related to fatigue. The ratings for the items are summed, indicating the level of severity of the symptoms. All the instruments (SDO-13, OBQ11, Oval-pd, WAI, LiSat, EQ VAS, RAND-36, GSE-10, PSS-10, MFS) are reliable and valid, and higher scores on (all of) the assessments indicate greater/higher levels of experience with the assessed aspect. The self-reported assessments (OBQ11, Oval-pd, WAI, self-estimated work ability/sick leave, LiSat, EQ VAS, RAND-36, GSE-10, PSS and MFS) will be sent by mail with return envelopes for participants’ responses. Once the researcher receives the responses, a video meeting will be arranged to conduct the SDO interview. Data on sociodemographic and care received during the study period will also be collected.

#### Acceptability and value of SEE 2.0

Client acceptability of SEE 2.0 components and perceived value will be assessed using study-specific self-report forms.^31^ In conjunction with the forms, potential harm will be assessed with an open-ended written question. These forms will be included in the postal questionnaire sent out for the 4-month assessments.

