## Ethics and dissemination

The project has been approved by the Swedish Ethical Review Authority (EPM Dnr: 2023-08032-01, 2024-042277-02, 2025-00635-02, 2025-04193-02) and will be conducted in accordance with the Declaration of Helsinki,^67^ the Swedish law of ethical research on humans^68^ and the GDPR.^65^ All participants will receive information about what participation in the research means both orally and in writing and can ask questions before they sign the written informed consent form and send it to the researchers. This includes information about the potential benefits or risks of participation and the right to withdraw their participation in the study at any time without explanation. They will also be informed that the data will be treated as confidential. Given the small sample size from a local perspective, the amount of personal information will be limited to ensure that participants’ identities cannot be derived from study presentations as in scientific papers.

During the implementation of the internet-based intervention SEE 2.0, patient safety and the protection of sensitive data are ensured by using the support and treatment platform on Sweden’s 1177 National Healthcare Guide. Logging in to the platform is performed via national e-identification. Based on person-centredness, clients can choose whether to carry out the guiding dialogues that support their change process digitally or via personal meetings at the healthcare settings. For digital meetings, secure forums recommended by the organisation will be used. The researchers will not have access to 1177 or medical records.

The results will be presented at conferences that attract researchers, professionals and the general public. Particular emphasis will be placed on reaching out to interest groups (such as patient and professional associations). The studies will be published in international scientific journals, and the researchers will adhere to established authorship guidelines. Popular science summaries of the results will also be created for various audiences and shared on the LTU website and social media.

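### Harm is asked about explicitly only once, in the 4-month postal pack, so harms in early leavers and after 4 months may be under-recorded and acceptability may look too favourable

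*Protocol article*

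**What the plan says.** The section on acceptability and value of SEE 2.0 describes study-specific client self-report forms and adds: "In conjunction with the forms, potential harm will be assessed with an open-ended written question". It then fixes timing and mode: "These forms will be included in the postal questionnaire sent out for the 4-month assessments". The Data collection section gives the same single time point for the ratings: "Additionally, at 4 months, clients will rate the acceptability and value of SEE 2.0".

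Follow-up is longer than that. Under Participant timeline, "evaluations will be conducted 4 months and 12 months after the start of SEE 2.0". The intervention is expected to take 2 to 4 months, and both that section and the description of the client programme expect clients' change to continue afterwards.

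The section on enrolment and retention has drop-out measured as a rate and does not mention reasons. The Data analysis section states an intention-to-treat approach and a descriptive compilation of potential harms. The ethics section says that the researchers have no access to the treatment platform or to medical records.

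**The concern.** A question asked once, by post, at a fixed time is answered only by people who are still in the study then and who send the pack back. Clients who find the programme burdensome or harmful are plausibly less likely to do either. If so, the recorded harms would be too few and the acceptability ratings too favourable. Harm that emerges or is recognised after 4 months has no stated question to catch it, although the plan expects change to go on beyond the programme.

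Client acceptability and value form the third listed objective, and the abstract says that the results will guide whether a full-scale evaluation is planned. A favourable picture produced by selective return would feed directly into that decision.

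**Working it through.** **Step 1: the stated channels side by side.** The article gives no figure for harm or return, so there is nothing to reproduce. The first check is of the text.

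| Channel (section) | Stated to ask about harm? | Reach among early leavers and after 4 months |
|---|---|---|
| 4-month postal forms (Acceptability and value) | Yes | Only those who are sent and return the pack; no repeat |
| Client interviews (Client experiences) | No | 6–12 selected clients, at 1 month and after completion (4–5 months) |
| Structured OT interviews (Intervention adherence) | No; the purpose is adherence | Held when phase 4 and the intervention are completed; as worded, a client who leaves before phase 4 reaches neither |
| Researcher field notes (Intervention adherence) | No; feasibility, adherence, implementation | Depend on meetings taking place |
| Video meeting for the SDO interview (Suitability and acceptability of outcome assessments) | No | Arranged only after the postal responses arrive |
| Focus groups (OTs' and professionals' experiences) | No; acceptability is a topic | Staff views, not those of individual leavers |
| 12-month outcome scales (same section as the SDO interview) | No | Could show worsening, but without a control group it cannot be attributed to SEE |

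The interviews cover between 6/40 = 15% and 12/30 = 40% of clients. The interval with no stated harm question is 12 − 4 = 8 months.

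**Step 2: illustration of size.** The sample size is from the article: "The estimated number of client participants required to achieve the study objective is 30–40". The non-return rates of 10–30% are assumptions. With zero harms among n returned forms, the one-sided 95% upper limit is 1 − 0.05^(1/n).

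| Clients | Assumed non-return | No answer | Returned (n) | Upper limit if no harm reported |
|---|---|---|---|---|
| 30 | 0% | 0 | 30 | 9.5% |
| 30 | 10% | 3 | 27 | 10.5% |
| 30 | 20% | 6 | 24 | 11.7% |
| 30 | 30% | 9 | 21 | 13.3% |
| 40 | 0% | 0 | 40 | 7.2% |
| 40 | 10% | 4 | 36 | 8.0% |
| 40 | 20% | 8 | 32 | 8.9% |
| 40 | 30% | 12 | 28 | 10.1% |

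Most of each limit comes from the small sample. The limits also hold for all clients only if non-return is unrelated to harm.

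**Step 3: selective non-return.** Assume a true harm rate p = 0.10 and let a share s of harmed clients fail to return the pack. The chance of recording at least one harm is 1 − (1 − p(1 − s))^N.

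| s (assumed) | N = 30 | N = 40 |
|---|---|---|
| 0 | 1 − 0.90^30 = 95.8% | 1 − 0.90^40 = 98.5% |
| 0.5 | 1 − 0.95^30 = 78.5% | 1 − 0.95^40 = 87.1% |
| 0.8 | 1 − 0.98^30 = 45.5% | 1 − 0.98^40 = 55.4% |

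Selective loss matters more than the modest widening of the limits in Step 2.

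**The case against.** A reader might infer that early leavers are never asked and that their harms are lost. The documents do not support that. Stopping SEE is not the same as leaving the study. Intention to treat is stated, and nothing says that a client who stops SEE but stays in the study is not sent the 4-month pack. Nor does the text say that such a client is sent it.

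A reader might also infer that clients are asked nothing at 12 months. That is wrong: stress, fatigue, health, work ability and activity measures are repeated then, and data on care received during the study are collected. Only a harm question is absent.

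Acceptability and burden can also surface in the interviews, field notes and focus groups, and drop-out is itself a reported feasibility result. An upward bias in acceptability is therefore plausible but not shown. The content of the OT registration form and the supplementary timeline table are not reproduced, so it cannot be said that OTs are excluded as a source of harm reports. Finally, this is a small, uncontrolled feasibility study that does include a harm question and does not claim to estimate a harm rate.

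These points limit how strongly the concern can be put. They do not remove it. The article itself fixes the single time point and the postal mode, so this is more than detail left to a fuller document. No other described channel is stated to ask about harm, and several depend on completing a stage or returning the pack.

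**Conclusion.** The concern holds in a limited form. Harm is explicitly solicited once, at 4 months, by post, and client acceptability and value are rated only in the same pack. No harm question is stated at 12 months or when a client stops. Harms in early leavers and harms after 4 months may be under-recorded, and acceptability may look more favourable than it is.

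The size cannot be derived from the article. Under the assumed 10–30% non-return, 3–9 of 30 or 4–12 of 40 clients give no answer. Under an assumed 10% harm rate with 50–80% of harmed clients not returning the pack, the chance of recording any harm drops to 78.5–45.5% with 30 clients and 87.1–55.4% with 40. The direction rests on the assumption that dissatisfied or harmed clients return the pack less often.

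**What to change.** 1. Repeat the open harm question in the existing 12-month postal pack.
2. State that clients who stop SEE but stay in the study are still sent the 4-month harm, acceptability and value forms.
3. Offer clients who leave the study a short exit version of these forms. It must be voluntary, because participants are told of "the right to withdraw their participation in the study at any time without explanation".
4. Report harms and acceptability with the number who started SEE, the number who answered and the number who did not, so that silence is not read as absence of harm.

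The cost is one reused question, one short form and a small ethics amendment. Coverage will be partial. Enrolment began in September 2024, so the first clients were due at 4 months around January 2025 and at 12 months around September 2025, and some may already have passed these points. The report should say from when the added questions applied.
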